## Abstract

**Background: **Changes in intestinal mucosal integrity and gut microbial balance occur in severe acute malnutrition (SAM), resulting in treatment failure and adverse clinical outcomes (gram-negative sepsis, diarrhoea and high case-fatality). Transient lactose intolerance, due to loss of intestinal brush border lactase, also complicates SAM, thus milk based feeds may not be optimal for nutritional rehabilitation. Since the gut epithelial barrier can be supported by short chain fatty acids, derived from microbiota fermentation by particular fermentable carbohydrates, we postulated that an energy-dense nutritional feed comprising of legume-based fermentable carbohydrates, incorporated with lactose-free versions of standard World Health Organization (WHO) F75/F100 nutritional feeds will enhance epithelial barrier function in malnourished children, reduce and promote resolution of diarrhoea and improve overall outcome.

**Methods:** We will investigate in an open-label trial in 160 Ugandan children with SAM, defined by mid-upper arm circumference <11.5cm and/or presence of kwashiorkor. Children will be randomised to a lactose-free, chickpea-enriched feed containing 2 kcal/ml, provided in quantities to match usual energy provision (experimental) or WHO standard treatment F75 (0.75 kcal/ml) and F100 (1 kcal/ml) feeds on a 1:1 basis, conducted at Mbale Regional Referral Hospital nutritional rehabilitation unit. The primary outcomes are change in MUAC at day 90 and survival to day 90. Secondary outcomes include: i) moderate to good weight gain (>5 g/kg/day), ii)
*de novo* development of diarrhoea (>3 loose stools/day), iii) time to diarrhoea resolution (if >3 loose stools/day), and iv) time to oedema resolution (if kwashiorkor) and change in intestinal biomarkers (faecal calprotectin).

**Discussion:** We hypothesize that, if introduced early in the management of malnutrition, such lactose-free, fermentable carbohydrate-based feeds, could safely and cheaply improve global outcome by reducing lactose intolerance-related diarrhoea, improving mucosal integrity and enhancing immunity, and limiting the risk of systemic infection and associated broad-spectrum antibiotic resistance.

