### Study population

160 children aged > 6 months to 5 years.
*Inclusion criteria:* signs of severe malnutrition one of (i) Marasmus (defined by mid-upper arm circumference (MUAC) <11.5cm) and/or Kwashiorkor (defined as symmetrical pitting oedema involving at least the feet irrespective of WHZ score or MUAC) and a guardian or parent willing/able to provide consent.
*Exclusion criteria:* children with severe acute malnutrition with a very high risk of death due to a comorbidity e.g. malignant disease or terminal illness will be excluded.

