### Sample size

Mid-upper arm circumference (MUAC) has been selected as the primary criterion for nutritional recovery because it predicts mortality better and is less affected by oedema than other anthropometric measures, and is also a good index of muscle mass. A recent trial of antimicrobial prophylaxis in Kenyan children admitted with severe malnutrition baseline mean MUAC was 10.6 cm (SD 1.06) and at 90 days, 12.2 cm (SD 1.35), a mean change of 1.6 cm (SD 1.1) nutritional recovery at 90 days
^22^. The overall sample size will be 160 children which will include 80 in each study arm. From the original MIMBLE trial, safety in the study arms were comparable to the standard intervention (manuscript in preparation). As a Phase II study, this study is designed to provide adequate proof of principal that the modified nutritional feed provides clinical, physiological and biological evidence of benefit to the child in terms of nutritional rehabilitation and the predicted effect on biological markers of gut-barrier dysfunction and on the intestinal microbiota. Additionally, it will compare the safety and tolerability of the modified nutritional feed against the current standard of care. The data will thus inform the design and effect size for future pragmatic trials. Formal sample sizes were not calculated; since the study was designed to provide safety data and some indication of the likely efficacy of the modified feed compared to standard of care. We thus aimed to study 160 children in total, which is realistic given the timeframe and funding available for the study. 

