### Data management and statistical analysis

Information will be stored securely and will only be made available to those caring for the child and those directly involved in the study. Any reports will not mention the names of the child or parent/guardian. Patient admission data collection forms and observation charts will be kept in a locked cupboard. Designated members of the research team will transcribe relevant data from the source documents to the CRF. Data entry will be done through
OpenClinica, an FDA-approved, web-based application, to a relational PostgreSQL database. Security is enforced through authentication of users by use of encrypted passwords. Different access level accounts authorize users on actions they may perform on the database.

Data will be analysed on an intention-to-treat basis. Differences in outcome measures between the three treatment groups will be compared with ANOVA or linear regression as appropriate. Where variables are not normally distributed, they will be transformed by taking logarithms. If this is insufficient, then equivalent non-parametric tests will be used. Metabolomic data will be analysed using multivariate statistical techniques including principal components analysis, projection to latent structures (PLS) and orthogonal PLS.

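### The log-if-not-normal rule has no exception for change scores, so it cannot be applied as written to the co-primary MUAC change and leaves the data to choose the effect scale

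*Protocol article*

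**What the plan says.** The section on co-primary outcome measures lists two: survival to day 90 and, in the Abstract's words, "change in MUAC at day 90". The section on secondary outcomes adds changes in intestinal biomarkers, namely faecal calprotectin.

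The analysis of all of these is set out in one paragraph of Data management and statistical analysis:

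- Population: "Data will be analysed on an intention-to-treat basis".
- Model: outcome differences "will be compared with ANOVA or linear regression as appropriate". No covariate is named and none is excluded.
- Transformation: "Where variables are not normally distributed, they will be transformed by taking logarithms".
- Fallback: "If this is insufficient, then equivalent non-parametric tests will be used".

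The paragraph has no exception for variables that can be zero or negative, and no criterion for when the log step counts as insufficient.

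The Sample size section cites an earlier trial in Kenyan children with severe malnutrition. It gives MUAC at baseline (mean 10.6 cm, SD 1.06), MUAC at day 90 (12.2 cm, SD 1.35) and "a mean change of 1.6 cm (SD 1.1) nutritional recovery at 90 days". The same section says that the data are meant to guide the effect size of later trials.

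**The concern.** A change in MUAC is a difference between two measurements and is not positive when a child fails to gain. For such a child the prescribed transformation has no value. The Study population section also admits children on the basis of "symmetrical pitting oedema involving at least the feet irrespective of WHZ score or MUAC", so some may enter with less MUAC to regain.

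If the change were judged non-normal, the protocol would offer no workable next step on that variable. The analyst could drop the undefined values, add a constant, log MUAC before differencing, or go straight to a rank test. Each choice would be made after seeing the data. Dropping non-gainers would also conflict with the intention-to-treat statement in the same paragraph.

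The sequence also leaves the estimand open. It can end in a mean difference in cm, a ratio or a rank comparison, and these are three different effects. A rank test alone gives no difference in mean MUAC to plan a later trial with.

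For calprotectin the issue is sharper if the change is taken as a difference. The Objectives section hopes for benefit on gut inflammation, so a fall, which is a negative change, is the desired result.

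**Working it through.** **Inputs.** From Sample size: baseline SD 1.06, day-90 SD 1.35, mean change 1.6, SD of change 1.1 (all cm), 80 children per arm. The article states that no formal sample size calculation was made, so there is no power figure to reproduce. The cited means are consistent with each other: 12.2 − 10.6 = 1.6 cm.

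**1. How many changes would have no logarithm?**
- Normal approximation: P(change ≤ 0) = Φ(−1.6/1.1) = Φ(−1.455) = 0.073.
- Counts: 0.073 × 160 = 11.7 children, or 5.8 per arm of 80, if every child were measured and both arms had the cited mean.
- Rounding: with the mean between 1.55 and 1.65 and the SD between 1.05 and 1.15, the proportion runs from 5.8% to 8.9% (9 to 14 of 160).
- Without a shape assumption, the one-sided Chebyshev bound gives only an upper limit: 1.1²/(1.1² + 1.6²) = 1.21/3.77 = 32%. The lower limit is zero.

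**2. What if the undefined values were dropped?** This is one possible improvisation and the article does not prescribe it. Assume a true benefit of 0.5 cm, so means of 1.6 and 2.1 with SD 1.1.
- Children lost per 80: control 80 × Φ(−1.6/1.1) = 5.8; experimental 80 × Φ(−2.1/1.1) = 2.3.
- Mean of those kept = m + s·φ(m/s)/Φ(m/s): control 1.764, experimental 2.173.
- Remaining difference on the cm scale: 0.41 cm instead of 0.50. The same calculation for a true 0.3 cm leaves 0.24 cm.

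**3. What would baseline adjustment add?**
- Implied correlation of baseline and day-90 MUAC: r = (1.06² + 1.35² − 1.1²)/(2 × 1.06 × 1.35) = 0.607.
- Residual SD after adjustment: 1.35 × √(1 − 0.607²) = 1.073 cm, against 1.10 for the raw change.
- Variance ratio: 1.073²/1.10² = 0.952, a gain of about 5% (3% to 7% if the SD of change is 1.05 to 1.15).
- Standard error with 80 per arm: 1.10 × √(2/80) = 0.174 cm falls to 1.073 × √(2/80) = 0.170 cm. The 95% CI half-width falls from 0.34 to 0.33 cm.
- Implied regression slope on baseline: 0.607 × 1.35/1.06 = 0.77. A change score fixes this slope at 1.0, so it over-corrects by 0.23 cm for each cm of baseline imbalance. A one-standard-error imbalance is 1.06 × √(2/80) = 0.168 cm, which shifts the estimate by 0.23 × 0.168 = 0.04 cm.

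**The case against.** The strongest reply is that the paragraph contains its own safeguard. A log that cannot be computed is naturally insufficient, so the rank-test step follows, and a rank test keeps zero and negative changes. The rule also speaks of variables, so MUAC itself, which is always positive, could be what is logged. For calprotectin, logging the values rather than their difference fits the text equally well. All of this stands, and it makes any loss of children conditional. It does not say which route is to be taken, and each route gives a different effect scale.

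A second reply is that the 7% undercuts itself: under the normal model that produces it, the log rule would not be triggered, and with the right skew that usually prompts a log the lower tail would typically be thinner. That is also fair. The figure shows that non-positive changes are to be expected at this mean and SD. It does not forecast exclusions.

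Three stronger readings are tempting, and the document does not support them:

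- **That the MUAC comparison is unadjusted.** The text allows linear regression and is silent on covariates, which a protocol article commonly leaves to the analysis plan.
- **That much precision is lost.** On the cited SDs the gain from adjustment is about 5% of variance. No figure in the article shows how far oedema at entry would add to it.
- **That the worst outcomes will drop out.** Nothing says that non-gainers are excluded. Children who die have no day-90 MUAC on any scale, and survival is a separate co-primary outcome.

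It can also be said that this is a phase II pilot, that a later phase III trial would have mortality as its primary endpoint, and that a difference in cm can be reported whatever test is used. This lowers the stakes, but it does not fix the primary analysis.

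**Conclusion.** The point holds in a limited form. The stated transformation rule reaches a signed co-primary outcome to which it cannot be applied when MUAC does not rise. On the cited figures that is roughly 7% of measured children (5.8% to 8.9% over rounding). If the rule were triggered, the analysis would be improvised or would fall to a rank test, and the data would choose the effect scale. With about 80 per arm, a comparison of means does not need normally distributed raw values, so the switching offers little in return.

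Baseline adjustment belongs to the remedy. The text leaves it open, so its absence is not an error. Its benefit is small in precision and modest in protection against chance imbalance.

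The figures rest on the external trial's means and SDs, a normal approximation, and complete measurement at day 90. The assumed 0.5 and 0.3 cm benefits are illustrations. Importance is moderate: it should be settled before the data are analysed, and it does not put the design in doubt.

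**What to change.** 1. State that the log rule does not apply to change scores.
2. Fix one primary MUAC analysis among children measured at day 90: linear regression of day-90 MUAC in cm on arm and baseline MUAC, reported as a difference in cm with a 95% CI. Oedema at entry may be added as a covariate. No test of normality should alter this analysis; a rank test can be kept as a sensitivity analysis.
3. For faecal calprotectin, model the log of the follow-up value adjusted for the log of the baseline value, in place of any log of a change.

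The cost is a few sentences. Baseline MUAC, oedema status and the stool samples are already part of the planned data collection, and neither sample size nor visits change. If an analysis plan exists and already fixes these points, it is enough to bring the article's wording into line with it.

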### Ethical statement

Ethical and regulatory approval has been granted by Imperial College Research Ethics Committee (17IC4146), the sponsor of the study and from Mbale Regional Hospital Institutional Review Committee (019/2018) and UNCST (HS2391). The MIMBLE2 study has been registered on ISRCTN (registry identifier
10309022).

### Safety

There are very few risks attached to this study. Intolerance or allergy to chickpeas are rare. Details of the processing and packaging will be addressed by due diligence of the experienced collaborator (Campden BRI).

Blood samples are required as part of this study; this includes routine blood sampling according national guidelines and an additional 12 ml over the whole duration of the study. Required volumes of blood will be minimized wherever possible and be within the locally agreed maximum. Urine and stool will be collected in a non-invasive manner thus should not cause any distress to the child or their family.

Potential benefit to the child and/or family include:

• Closer observation during admission, which consequently may allow the clinical team to make-important changes to the child’s treatment during in hospital stay.

• All routine non-study medications required by the hospital to treat the child will be made available. Any additional procedure required due to a complication or a potential complication will be covered by the study.

• The parents or guardians for the children will be asked to return for follow up at 28 days after admission. This additional visit will include a clinical review thus an opportunity for medical treatment if required. Education regarding nutrition will also be readdressed at this time. Reimbursement for transport cost for this follow-up visit plus any treatment costs required during the visits will be made.

### Protocol version changes

Version 1. Previous versions approved the use of locally sourced legumes which could not be certified to the same standards as those in the UK.

Version 2. First version included another recruitment site, which became unfeasible.

We do not anticipate any changes to the design of the trial; however, if there were need to alter the trial (e.g., a request for an extension in enrolment, changes or addition of a trial centre and/or investigators), this would be communicated to the ICREC, MRRHREC and UNCST via a formal request for a protocol amendment, as would any other changes in the trial protocol.

## Discussion

Prior to this study we conducted a proof-of-concept study in East Africa in undernourished children MIMbLe Study (Pan African Clinical Trial Registry:
PACTR201805003381361) using locally developed cowpea flour added to standard nutritional feeds. We were reassured by the safety and tolerability of this feed. In addition, cowpea-enhanced feeds resulted in a positive effect on increasing bacterial diversity and a favourable decrease in anorectic gut hormones. This led to further funding to enable product development and testing in a randomised control trial. Initially cowpea was targeted as a locally available legume that contains adequate amounts of the resistant starch of interest to promote gut microbial health. The legume-based interventions we propose are used within the local diets but have been milled/processed in such a way to maximise their ability to ferment within the bowel to create a favourable microbiome. The details of the manufacturing process and details of the final product will be available on request (manuscript in preparation).

During the 6-month period of product development we encountered two significant barriers to utilising cowpeas in the current study. First, on testing, a final cowpea-enriched feed product was found to have significantly less resistant starch than anticipated, and second we were not able to identify a commercial supplier whose products met the strict food safety standards required with respect to certification for contaminants including pesticides, toxins, microbes and metals. We therefore opted to use another locally available legume alternative, the chickpea, although this is eaten less frequently in Uganda. On testing we found that the final nutritional paste retained its resistant starch content throughout processing, moreover chickpea (gram) flour was readily available from reputable suppliers. Overall, chickpea production in Uganda in 2016 was estimated to be 5085 tonnes in 2016 by the Food and Agricultural Organization of the United Nations, increasing by approximately 100 tonnes (2.2%) each year since 2010. The safety is assured as intolerance or allergy to chick peas are rare. The G6PD variant in these populations retains >12% of its activity, thus not rendering G6PD-deficient patients to susceptibility to oxidant stress (as seen in Mediterranean variants rendering them susceptible to ‘Favism’)
^23^.

### Potential future impact

An increasing awareness that malnourished populations have higher levels of gut dysfunction with frequent episodes of infection, and a focus on both carbohydrate and protein requirement is inescapable. Enhancing carbohydrate delivery to the colon offers a solution to supporting a mature and diverse microbiome whilst simultaneously promoting gut integrity through SCFA production, together with improving plant-based protein digestibility and bioavailability are both relevant in any attempt to promote greater production and consumption of pulses. Enhancing these qualities in legumes thus offers affordable, scalable and enhanced health management to a very large number of undernourished children. The current phase II trial, if successful, will generate clinical and biological endpoints that will help inform the design and sample size of a future phase III trial with mortality as the primary endpoint.

### Study progress

The modified feed was developed between August 2017 and March 2018. The final product has passed a full microbiological sterility testing following a pre-incubation at 30°C for 14 days, and an incubation on different culture media at 25°C, 37°C and 55°C for a further 7 days. The product is also confirmed to contain <40 µg/kg acrylamide, <400 HAU/g lectin, and <50 mg/kg tin, and was transported to Uganda in June 2018. 

### Recruitment status

The trial started enrolment on 6
^th^ July 2018 and will recruit over a period of 4–6 months. Primary data analysis and report-writing will take a further 4–6 months.

## Data availability

All data underlying the results are available as part of the article and no additional source data are required.
